#### Secondary outcomes

ADAPT CP secondary outcomes will address the following domains: acceptability, adoption, appropriateness, feasibility, fidelity, cost and penetration, and sustainability of the ADAPT CP, defined in large part by the Proctor framework of implementation outcomes [33] (see detail below and in Table 1). ADAPT implementation strategy outcomes will address similar domains, but with reference to the degree to which implementation strategies (Awareness Campaigns, Champions, Academic Detailing and Support, Education, Reporting and Technology) support the implementation of the ADAPT CP.

*Acceptability is* operationalised as the perception of cancer service staff that the ADAPT CP (1) and the ADAPT implementation strategies (2) are agreeable, palatable and satisfactory, the first in addressing anxiety and depression in their client population, the second in facilitating implementation. This will be measured qualitatively during staff interviews.

*Adoption* of the ADAPT CP (1) is operationalised as the proportion of patients at each site who are registered and screened on the ADAPT Portal. Adoption of the ADAPT implementation strategies (2), is operationalised as mean staff ratings of how much they were aware of, observed and used each implementation strategy, collected via the staff questionnaire.

*Appropriateness* is operationalised as the extent to which staff believe that the ADAPT CP has fit, relevance and compatibility at the level of their setting, their role, and the needs of their consumers, measured quantitatively by the Hands 4 U questionnaire [34] (items adapted to the context of this study) and additional study-developed items within the staff questionnaire. Appropriateness will also be measured qualitatively in staff interviews.

*Feasibility*, operationalised as the extent to which the ADAPT CP is considered feasible by staff of each service, given their different needs and resources, and the degree of individual tailoring required to set up the ADAPT Portal, will be measured qualitatively in semi-structured interviews.

*Direct costs* of delivering the ADAPT implementation strategies (in terms of research staff time and resources) will be calculated from the research team logs. Costs of developing, maintaining and delivering different components of the ADAPT CP, will also be calculated. Patient health services use, including pharmaceutical prescriptions related to anxiety and depression, will be extracted from Medicare MBS/PBS and hospital medical records data. These data will be used to estimate changes in health system resource use before and after participating in the ADAPT CP, and to determine whether differences in adherence are associated with differences in health system resource use and overall costs.

*Penetration* is operationalised as the number of staff and services who were aware of, and engaged with, the ADAPT CP and implementation strategies.

*Sustainability*, defined as the extent to which the ADAPT CP is maintained or institutionalized within a service setting’s ongoing, stable operations, will not be measured during the ADAPT Cluster RCT, as no data will be collected beyond the 12 months implementation phase. However, intention to sustain the ADAPT CP will be elicited during T2 qualitative interviews. Further funding will be sought to audit actual sustainability in the future at participating sites, post the RCT.

**Predictors of adherence**, including staff attitudes to the ADAPT CP, perceived social influence to enact it, self-efficacy, organisational readiness and intention to implement the ADAPT CP, will be assessed by the Organisational Readiness to Change (ORIC) questionnaire [35], Hands4U questionnaire [34] and some study-developed ADAPT organisational readiness items.

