### Hypotheses

(Note, methods used to measure each outcome referred to in the hypotheses are described in the Measures sub-section of the Methods and design section below.)

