#### Secondary hypotheses

Adherence to the ADAPT CP and predictors of adherenceAdherence to each component of the ADAPT CP (yes/no) will be greater in the Enhanced implementation arm than in the Core implementation arm.Adherence to the ADAPT CP will increase from the 6- to 12-month follow-up.Staff-perceived individual and site readiness to change will be associated with adherence to the ADAPT CP.Staff use of the ADAPT resources will be associated with adherence to the ADAPT CP.Characteristics of the service (size, psychosocial staffing, existing psychosocial screening), will influence staff attitudes and adherence to the ADAPT CP.Greater awareness/use and perceived utility of implementation strategies will be associated with better adherence to the ADAPT CP.Acceptability of the ADAPT CP and resources7.The ADAPT CP will be acceptable to staff and patients.8.At least 60% of staff will be aware of, use, and rate as useful, the ADAPT resources (including the health professional training and the ADAPT Portal).ADAPT implementation strategies (Core and Enhanced)9.Both Core and Enhanced ADAPT implementation strategies will be feasible (delivered) and delivered with fidelity as planned.10.At least 60% of staff will be aware of, use, and rate as useful, both Core and Enhanced ADAPT implementation strategies.11.Acceptability, adoption, appropriateness, feasibility, fidelity, and penetration of implementation strategies will be greater in the Enhanced implementation arm than the Core implementation arm.12.Improvements in staff-reported acceptability of the ADAPT CP and perceived readiness to change will be greater at 6- and 12-month follow-ups in the Enhanced implementation arm compared to the Core implementation arm.Cost-effectiveness13.While more costly, the Enhanced implementation arm will achieve greater adherence than the Core implementation arm.Patient outcomes14.Anxiety and depression screening scores at rescreening will be significantly lower than at the initial screen.

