### Study procedures and timeline

Randomisation will be performed by the study statistician using online randomisation software (STATA). Allocation concealment will be preserved; both sites and ADAPT Program staff conducting assessments will remain blinded until study completion. Following randomisation, sites will undertake a 3-month period of engagement to clarify study procedures, train staff in the ADAPT CP and use of the ADAPT resources, and tailor the ADAPT Portal to local site resources and preferences. Study sites will then complete baseline (T0) staff questionnaires and interviews to ascertain staff views on service and staff readiness to adopt the ADAPT CP. The online questionnaires will be available on RedCap (Research Electronic Data Capture) [29] and automatically downloaded to a database to reduce possible bias. The ADAPT research team will follow-up those participants who do not complete or return their questionnaire within 2 weeks, with up to three reminder emails or phone calls at different times of the day. A subset of staff with key roles in implementing the ADAPT CP will be invited to participate in an audio-recorded semi-structured interview exploring their views of the ADAPT CP, barriers and facilitators to its use and site readiness.

Sites will then “go-live,” integrating the ADAPT CP into clinical care for a 12-month implementation period. Staff will be encouraged to introduce the ADAPT CP to all patients as part of routine care, and on their verbal consent, register them into the ADAPT Portal. Patients will then be asked to access the ADAPT Portal for efficient screening and data collection, information and access to ADAPT resources. Staff will be asked to respond to ADAPT emails and alerts for patients who require further assessment and referral. ADAPT research staff will administer Core versus Enhanced implementation strategies as per randomisation during this period.

Mid-way through the 12-month implementation period (T1 at 6 months) and at the end of the implementation period (T2 at 12 months), questionnaire data will again be collected from cancer service staff, and a subset of cancer service staff will participate in an audio-recorded semi-structured interview to ascertain staff views on implementation outcomes, and awareness of and perceived utility of the ADAPT CP implementation strategies.

Timing of enrolment, engagement, intervention and data collection is shown in Table 2.

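### Penetration has no denominator, staff acceptability is interview-only, and patient acceptability has no named measure, so the parts of secondary hypotheses 7, 11 and 12 that rest on them cannot be tested as written

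*Protocol article*

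**What the plan says.** The note under Hypotheses tells the reader that "methods used to measure each outcome referred to in the hypotheses are described in the Measures sub-section". The article therefore points to its own Measures text for the outcome behind each hypothesis.

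Secondary outcomes gives this definition for acceptability: "operationalised as the perception of cancer service staff that the ADAPT CP (1) and the ADAPT implementation strategies (2) are agreeable, palatable and satisfactory". On how it will be assessed, the same entry says: "This will be measured qualitatively during staff interviews". Feasibility is likewise assessed in interviews. Study procedures and timeline limits who is interviewed at T0: "A subset of staff with key roles in implementing the ADAPT CP will be invited to participate in an audio-recorded semi-structured interview". At T1 and T2 a subset of staff is again interviewed, without a statement that it is the same people. Secondary analyses has interview data coded into themes. For penetration the definition reads: "operationalised as the number of staff and services who were aware of, and engaged with, the ADAPT CP and implementation strategies".

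The Secondary hypotheses ask more of these measures:

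- Hypothesis 7: "The ADAPT CP will be acceptable to staff and patients". Objective iii also covers patients.
- Hypothesis 11: six properties of the implementation strategies, among them acceptability, feasibility and penetration, will be greater in the Enhanced arm.
- Hypothesis 12, which sets Enhanced against Core, reads: "Improvements in staff-reported acceptability of the ADAPT CP and perceived readiness to change will be greater at 6- and 12-month follow-ups in the Enhanced".
- Hypothesis 14: "Anxiety and depression screening scores at rescreening will be significantly lower than at the initial screen".

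**The concern.** A directional comparison between randomised arms needs a quantity that can be compared. Themes from interviews with selected key staff provide no score, and so no estimate of a difference or of a change. A head count can be compared, but it rises with the number of staff employed as well as with the share engaged. Sites may be whole services or single departments (Inclusion criteria), so staffing will vary. For patients, the Measures text names no acceptability outcome at all.

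If this is left alone, the measure behind several arm contrasts would have to be chosen after the data are seen, or the contrasts would be reported from material that cannot carry them. A penetration result could also be read as an effect of the Enhanced strategy when it reflects staffing.

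**Working it through.** **1. Figures in the plan.** The article gives no power or effect size for hypotheses 7, 11, 12 or 14. Its staff figure is internally consistent: 10 per site × 12 sites = 120. Six sites per arm (assumed) gives 60 staff per arm.

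**2. Each hypothesis part against its designated measure.**

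| Part | Measure in the article | Testable as stated? |
|---|---|---|
| H7, staff | Interviews; no criterion for acceptable | No criterion to test against |
| H7, patients | None named | No |
| H11, acceptability and feasibility | Interviews | No arm contrast possible |
| H11, adoption | Mean staff questionnaire ratings | Yes |
| H11, penetration | Number of staff and services | Confounded with staffing |
| H12, acceptability | Interviews | No score for change by arm |
| H12, readiness | ORIC, Hands4U and study items at T0, T1, T2 (Table 2) | Yes |
| H14 | Portal screening scores | Yes, as worded |

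Table 2 schedules acceptability at T0, T1 and T2 but adds no instrument.

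**3. Penetration.** Count = number of eligible staff × proportion engaged. The article does not give eligible staff per site, so these numbers are assumptions. With 60% engaged in both arms:

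- 60 vs 60 staff: 36 vs 36
- 60 vs 90 staff: 36 vs 54
- 60 vs 120 staff: 36 vs 72

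The error can also run the other way. A count of 36 in each arm is 36/60 = 60% in one and 36/90 = 40% in the other, so a real difference would be hidden. The services part of the count is less exposed, because the number of services is fixed at 12.

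**4. What a staff score could detect.** If hypothesis 12 used a questionnaire score with 10 staff per site, effective n per arm = 60 / (1 + 9 × ICC). The difference detectable with 80% power at two-sided 5% is (1.96 + 0.84) × √(2 / effective n). The ICCs are assumed:

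- ICC 0: n = 60, 0.51 SD
- ICC 0.05: n = 60/1.45 = 41.4, 0.62 SD
- ICC 0.10: n = 60/1.90 = 31.6, 0.71 SD

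Using t on 10 degrees of freedom for 12 sites, these become 0.57, 0.68 and 0.78 SD. Any gain from T0 adjustment is not included.

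**5. Hypothesis 14.** Suppose only patients above a cut-off at first screen were compared. With no true change, the expected fall is (1 − r) × φ(c)/p SD, where p is the proportion above the cut-off c and r the test-retest correlation. Take p from 20% to 36% (the range of moderate-to-severe figures in the sample size section) and r assumed from 0.5 to 0.8. The extremes are 0.5 × 1.40 = 0.70 SD (p = 20%, r = 0.5) and 0.2 × 1.04 = 0.21 SD (p = 36%, r = 0.8). If all patients are rescreened, the expected fall from this source is zero. Hypothesis 14 is not restricted to high scorers.

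**The case against.** The defence has real force on several points.

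- *The details may sit in the full protocol or SAP.* That would normally settle it, but the note under Hypotheses refers the reader to the article's own Measures text, so the mismatch is internal.
- *The design is openly mixed-methods, and hypotheses 8 and 10 set 60% criteria.* Qualitative appraisal of acceptability is legitimate. The 60% criteria do give numbers on awareness, use and usefulness of the resources and strategies. They are not designated as acceptability, and neither is an arm contrast, so they do not fill the gap in hypotheses 11 and 12.
- *Stratification by service size limits staffing imbalance.* It does, partly. It balances patient volume in two broad classes and does not equalise staff numbers. The documents do not support the stronger claim that a penetration comparison would mainly reflect staffing, since no site staffing figures are given.
- *The denominator is already collected.* True: staff are identified by organisation-chart mapping (Recruitment: cancer services and staff). This makes the fault cheap to mend.
- *Hypothesis 14 is sound.* A reader might infer that it would be confirmed even if nothing worked. The documents do not support that. The hypothesis makes no causal claim, objective vi is descriptive, and regression to the mean gives no expected fall if everyone is rescreened. What remains is that patients may defer or decline, so those rescreened may be a selected group.

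**Conclusion.** The point holds in a limited form. As written, four things cannot do what the hypotheses ask: patient acceptability (hypothesis 7, objective iii), staff acceptability as a change-by-arm contrast (hypothesis 12), acceptability and feasibility of the strategies as arm contrasts (hypothesis 11), and penetration as a raw count (hypothesis 11). The possible distortion in penetration depends on staffing imbalance the article does not state; a twofold imbalance, assumed for illustration, turns equal engagement into 36 against 72.

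A reader might infer that hypotheses 7, 11, 12 and 14 are untestable as a whole. They are not: readiness and adoption have questionnaire measures, and hypothesis 14 can be tested as worded. A reader might also want hypothesis 14 turned into a comparison of rescreen scores between arms. That should not be the remedy: rescreening is itself a component of the primary adherence outcome, so the comparison would condition on something the strategies aim to change, and adjusting for the initial score would not cure that.

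The primary outcome and its analysis are untouched.

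**What to change.** 1. **Penetration.** Define staff penetration as the proportion of eligible staff, as identified in the organisation-chart mapping, who were aware of and engaged with the pathway and the strategies. Compare that proportion between arms with site as the cluster, and state how eligible staff who return no data are counted.
2. **Hypothesis 12, acceptability.** Designate the staff-attitude scores on Hands4U, already collected at T0, T1 and T2, and compare arms adjusted for T0. The article lists attitudes jointly under ORIC, Hands4U and study items, so name the items used. Keep the interviews as thematic support.
3. **Hypothesis 11, acceptability and feasibility.** Restate these as qualitative findings. Hands4U and ORIC are described as measuring views of the pathway and readiness, not of the strategies, so they should not be substituted.
4. **Hypothesis 7 and objective iii.** Name the Portal record of declined and deferred screening as the patient measure and say that it is indirect, or remove patients from both. State what would count as acceptable to staff.
5. **Hypothesis 14.** Keep it, adding that an uncontrolled fall among rescreened patients cannot be attributed to the pathway or to either strategy.

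The cost is wording plus one or two models on data already planned. The price is that attitude stands in for acceptability in hypothesis 12, that about 120 staff detect only moderate to large differences, and that declining or deferring screening can have reasons other than acceptability.

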### Interventions/groups

Sites will be randomised to a Core implementation arm versus an Enhanced implementation arm to facilitate uptake of the ADAPT CP. All cancer services will receive access to, and training to support use of, the online resources developed to support ADAPT. These resources (described in detail above) are the:ADAPT PortalADAPT Health professional trainingADAPT Patient education materialsiCanADAPT Cognitive-behavioural Therapy

The Core implementation and Enhanced implementation arms will differ in the implementation strategies used to support the use of ADAPT CP at their cancer service. Specifically, these differences are:*Core:* These sites will receive implementation strategies consistent with usual roll out of a clinical pathway in the NSW health context, to inform staff of the ADAPT CP and enable them to initiate use of the ADAPT Portal and intervention resources. Once the ADAPT Portal is launched and the implementation phase has commenced, Core sites will receive reporting feedback and audit reports at 4 weekly intervals and additional support from the ADAPT team only at their request (a passive approach).*Enhanced:* These sites will receive the same implementation strategies as the core group, with the addition of more prolonged, active engagement of the ADAPT team, that will continue during the 12-month implementation phase. These additional strategies will include monthly meetings to identify training and support needs of local champions, additional awareness activities, audit and feedback reports prior to and midway through the implementation phase summarised and presented face-to-face by research staff to site staff, and other tailored strategies to address the specific barriers and facilitators in each site (an active approach).

The strategies, described in detail in Table 1, were developed by the research team, comprising experts in the fields of psycho-oncology and implementation science, cancer services leaders, and consumers. A literature review, NSW Health current implementation practices, and the ADAPT barriers and enablers study [23] guided the development of the strategies.

**Table 1 Tab1:** Implementation strategies

Strategy	Both Core and Enhanced implementation strategies arms	Enhanced implementation strategies arm *only*

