Awareness campaign	• Roadshow presentation by ADAPT staff at the site 8 weeks before “go-live” • Poster displayed prominently 4 weeks prior to and at “go-live,” (T0) • Email from site champion to all staff 1 week before “go-live” (T0)	• Additional posters at 4-monthly intervals during implementation • Newsletters emailed to site staff at 2, 4, 6, 9 and 12 months
Champions	• Champion identification and role definition • Provision of email templates for champion to send staff • Inclusion of champion contact details in all staff communication	• Additional proactive contact with Champions at monthly intervals to discuss progress, provide audit reports and discuss additional implementation strategies as needed
Academic detailing and support	• Sites provide with a written report summarising change readiness data from baseline staff interviews at T0 • Tailoring of the ADAPT Portal to site requirements during engagement meetings • Study close meeting with all key staff to discuss sustainability of the ADAPT CP	• Sites provided with a verbal report of these data, at T0, T1 and T2 • Quarterly review of ADAPT Portal configuration to confirm allocated responsibilities and service tailoring
Reporting	• Monthly written reports on Portal statistics	• Presentation and highlighting of issues from monthly reports in face-to-face meetings with site
Technological support	• IT support for the ADAPT Portal	

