The two levels of implementation effort tested here (Core implementation strategy versus Enhanced implementation strategy) include multiple types of implementation strategies, and it will not be possible to determine whether one versus another has had the greatest impact. However, we will be able to investigate potential mediators and moderators of intervention success, to guide hypotheses for investigation in future studies.

With an increased focus on implementation of evidence that has been costly to accrue, and the potential to improve patient outcomes immediately, clinical pathways are likely to form the basis for care in a growing number of health systems. Clinical Pathways have great potential for enhancing the translation of evidence into practice, however health system policy and planning require accurate data on the costs and size of implementation effort required to ensure their success. Armed with such data, health service administrators can better plan introduction of clinical pathways within current budget constraints. Thus, this study will provide information critical to improving healthcare outcomes.

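### Strategy costs are taken from research staff time and research logs, with no stated item for site staff time, so the Enhanced-minus-Core cost difference is likely understated

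*Protocol article*

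**What the plan says.** The direct-costs paragraph under Measures, Secondary outcomes, has three parts.

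- Delivery of the implementation strategies is costed "in terms of research staff time and resources) will be calculated from the research team logs".
- For the pathway itself: "Costs of developing, maintaining and delivering different components of the ADAPT CP, will also be calculated".
- Patient use of health services, including prescriptions for anxiety and depression, "will be extracted from Medicare MBS/PBS and hospital medical records data".

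Interventions/groups defines the arms by addition. Of Enhanced it says: "These sites will receive the same implementation strategies as the core group, with the addition of more prolonged, active engagement of the ADAPT team". Table 1 lists what is added, including "Additional proactive contact with Champions at monthly intervals" and "Presentation and highlighting of issues from monthly reports in face-to-face meetings with site", together with verbal reports of the readiness data at T0, T1 and T2 and a quarterly review of the Portal configuration. During implementation, Core sites get regular written reports, and further help only if they ask for it.

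The cost comparison is used in the primary objective, in secondary objectives iv and v, and in hypothesis 13: "While more costly, the Enhanced implementation arm will achieve greater adherence than the Core implementation arm". The Discussion names the intended user. With these data, "health service administrators can better plan introduction of clinical pathways within current budget constraints".

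**The concern.** A meeting between the research team and a site uses time on both sides, but the stated rule counts only the research side. Site time in strategies common to both arms largely cancels in the Core versus Enhanced difference. Site time in contacts that only Enhanced sites are scheduled to have does not cancel. The missing cost is therefore expected to be larger in Enhanced, and the incremental cost is pulled down in that arm's favour.

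The economic comparison is at stake. The study sets out to find how much implementation effort and cost is worth paying for, and the reader it has in mind is a health service whose own staff would sit in these meetings. Time not logged during the 12 months is hard to recover afterwards.

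**Working it through.** The article states no cost, unit cost or hour total for the strategies, so there is no figure to reproduce. The check has two parts.

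**Is site time picked up elsewhere?** Objective iv names the costs of the pathway and the costs of the two strategies separately, and the Secondary outcomes text also treats them as different objects. The pathway-component item is therefore not stated to include time spent in strategy contacts. Medicare claims and hospital records describe patient care, not staff meetings. The text after Table 2 lists the forms. Contact logs, strategy checklist and diaries are completed by programme staff, while site staff complete surveys. No record of site staff time is named.

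**Direction and possible size.** Write S for site staff cost in strategy contacts:

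true difference = research-side difference + (S in Enhanced − S in Core)

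The second term is positive unless on-request support and other site effort in Core match the scheduled Enhanced contacts.

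Extra site hours per Enhanced site over 12 months:

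H = 12·c + P·d·k + 3·d·k + 4·d·q

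Counts from Table 1: 12 champion contacts (one champion each), P separate report presentations, 3 verbal reports, 4 Portal reviews. Assumptions: c = hours per champion contact, d = hours per meeting, k = site attendees at presentations and verbal reports, q = site attendees at Portal reviews. The high value k = 10 borrows the minimum of 10 staff per site given under Power for secondary endpoints.

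P is itself unclear. Table 1 suggests up to 12. Interventions/groups speaks of presented feedback before and midway through implementation, so 2. If the monthly presentations are merged into the champion contacts, P = 0.

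| Scenario | c, d, k, q | P = 12 | P = 2 | P = 0 |
|---|---|---|---|---|
| Low | 0.25, 0.5, 2, 1 | 3 + 12 + 3 + 2 = 20 h | 3 + 2 + 3 + 2 = 10 h | 3 + 3 + 2 = 8 h |
| Middle | 0.5, 0.75, 5, 2 | 6 + 45 + 11.25 + 6 = 68.25 h | 6 + 7.5 + 11.25 + 6 = 30.75 h | 6 + 11.25 + 6 = 23.25 h |
| High | 1, 1, 10, 3 | 12 + 120 + 30 + 12 = 174 h | 12 + 20 + 30 + 12 = 74 h | 12 + 30 + 12 = 54 h |

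The range is 8 to 174 hours per site. With 12 sites split equally (6 Enhanced), that is 6 × 8 = 48 to 6 × 174 = 1,044 hours.

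Research hours for the same contacts, with one research staff member, are R = 12·c + (P + 7)·d.

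- No preparation time, P = 12: R = 3 + 9.5 = 12.5 h (low) and 12 + 19 = 31 h (high). H/R is 20/12.5 = 1.6 to 174/31 = 5.6.
- With 2 hours of research preparation per contact (assumed; 31 contacts when P = 12, 19 when P = 0), site time is between 8/(8 + 6.5 + 38) = 15% (low, P = 0) and 174/(174 + 31 + 62) = 65% (high, P = 12) of the combined extra hours.

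Tailored strategies, newsletters and extra posters are left out on both sides, because the article gives no basis for their time.

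**The case against.** The strongest reply is that the sentence costs delivery, and research staff do the delivering, so their logs are the natural source. The paragraph does not say that this line is the whole Core versus Enhanced cost. A journal article also commonly leaves costing perspective and resource lists to a fuller plan. The logs may already show who attended and for how long, and the word for resources could be read as wider than the research team.

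Part of this stands. The logs may hold the data, and the fix allows for that. But the article does more than stay silent: it states a cost basis and names a source, and neither of the other two items fills the gap. A wider reading of resources is possible, but the only named source is still the research team's logs.

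It is also fair that Core sites may spend unlogged time, on request or unaided. That makes the direction likely, not proven. To cancel the gap, such time would have to match the scheduled Enhanced contacts, against the design's contrast of passive and active support.

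Three stronger readings are tempting and not supported:

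- A reader might infer that the omitted time exceeds the counted time. The working gives anything from well below the research hours to several times them, depending on assumed preparation, attendance and whether meetings are merged.
- A reader might infer that administrators pay only the omitted part. In a roll-out they would also have to fund the facilitation that research staff provide in the trial, so the counted part matters to them too.
- A reader might infer that hypothesis 13 is in doubt on cost. It already expects Enhanced to be the dearer arm, and adding site time points the same way.

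**Conclusion.** The point holds as a likely understatement of the Enhanced-minus-Core strategy cost, arising from a stated costing rule. It bears on the cost-effectiveness part of the primary objective and on objectives iv and v. It does not touch the adherence outcome or its GEE analysis.

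The direction rests on Enhanced being Core plus scheduled contacts that need site staff, and on Core's on-request and unsupported site time not being as large. The size cannot be determined from the article. The 8 to 174 hours per Enhanced site is an illustration in which every duration and attendance figure is assumed and only the contact counts come from the document. It should not be turned into a cost ratio or a corrected cost per adherent patient. The change is worth making because the bias falls on a comparison in the primary objective and the remedy is cheap.

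**What to change.** In the direct-costs paragraph, define strategy delivery cost as research staff time and resources plus cancer-service staff time, champions included. In both arms, and including on-request support at Core sites, record attendee role and minutes for each strategy contact in the contact logs and strategy checklist already kept. If those forms already hold this, only the wording needs to change. Value the time at health-service salary rates, use the total for the Core versus Enhanced cost and cost-effectiveness comparison, and report the research-only figure as a sensitivity analysis.

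The cost is at most two fields on existing forms and a sentence of protocol text. The downside is slightly more logging, and Enhanced will look somewhat less favourable on cost.
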